### Data analysis

#### Quantitative data

Our primary analyses will be by intention to treat, with secondary analyses involving study completers only.

##### Estimating impact on viral suppression

We will use a logistic regression to compare the likelihood of viral suppression between the three study arms after year 1 and after year 2. We will estimate an unadjusted model and a model that includes prespecified covariates to adjust for baseline characteristics and improve precision. We will adjust for the following covariates: age, education, sex, baseline adherence, baseline WHO disease stage, baseline viral suppression, duration on ART, self-reported physical health, self-reported mental health, and HIV disclosure status.

Our main unadjusted model has the following form:
1$$ \Pr \left({y}_i\right)=\mathrm{expit}\left({\beta}_0+{\beta}_1T{1}_i+{\beta}_2T{2}_i+{\epsilon}_i\right) $$

and our main adjusted model has the following form:
2$$ \Pr \left({y}_i\right)=\mathrm{expit}\left({\beta}_0+{\beta}_1T{1}_i+{\beta}_2T{2}_i+{\boldsymbol{X}}_{\boldsymbol{i}}{\boldsymbol{\beta}}_{\mathbf{3}}+{\epsilon}_i\right) $$

where *y*_*i*_ is the probability of viral suppression of individual *i*, T1 is an indicator for treatment group 1, T2 is an indicator for treatment group 2, and *ϵ*_*i*_ is the idiosyncratic error. The coefficients of interest are *β*_1_ and *β*_2_. Equation 2 has the term ***X***_***i***_***β***_**3**_, which includes a vector of the prespecified covariates described above (***X***_***i***_) and the respective coefficients (***β***_**3**_). We will estimate the marginal difference (or risk difference) between each of the three study arms as the following:
$$ \mathbbm{E}\left[{y}_i\right|T1=1\left]-\mathbbm{E}\left[{y}_i\right|\mathrm{Control}=1\right] $$: Impact of treatment 1 on the outcome relative to the control group$$ \mathbbm{E}\left[{y}_i\right|T2=1\left]-\mathbbm{E}\left[{y}_i\right|\mathrm{Control}=1\right] $$: Impact of treatment 2 on the outcome relative to the control group$$ \mathbbm{E}\left[{y}_i\right|T2=1\left]-\mathbbm{E}\left[{y}_i\right|T1=1\right] $$: Impact of rewarding adherence relative to rewarding viral suppression

We will also estimate a model where we pool T1 and T2 (relative to the control group) to estimate the impact of lottery incentives more generally.

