**Methods/design:**

We will enroll 330 HIV-positive patients at Mildmay Hospital in Kampala, Uganda, into a 2-year randomized controlled trial. Participants will be randomized to one of three groups. The first intervention group (T1, *n* = 110) will be eligible for small lottery prizes based on timely clinic visits and demonstration of viral suppression. Group 2 (T2, *n* = 110) will be eligible for the same lottery prizes conditional on high adherence measured by a medication event management system (MEMS) cap. The control group (*n* = 110) will receive the usual standard of care. Adherence will be measured continuously throughout the intervention period and for 12 months post-intervention to evaluate effect persistence. Surveys will be conducted at baseline and then every 6 months. Viral loads will be measured annually. Primary outcomes are whether the viral load is detectable and MEMS-measured adherence. Secondary outcomes are the log-transformed viral load as a continuous measure and a binary measure for whether the person took at least 90% of their ART pills.

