### Randomization

Randomization in a 1:1:1 ratio will occur after participants are recruited but before they complete a baseline survey to ensure that group assignment does not influence the answers given. We will stratify random assignment by age (under 25 or over 25), sex, marital status (married/cohabiting or unmarried), low CD4 count (below 200 or above 200), and viral load (detectable or undetectable). Stratified randomization is achieved by generating a separate block for each combination of covariates after identifying which clients fall into each block. We will then randomize treatment assignment within each block. We will use the *randtreat* package in Stata15 for the randomization procedure.

All clients recruited will complete the baseline survey approximately 2–3 months after recruitment. The client will be informed of their assignment to either one of the two intervention arms or the control group after completing the baseline survey.

Participants cannot be blinded to their treatment status and neither can interviewers. Interviewers are not blinded to treatment status when they read a MEMS cap. The data analyst who will conduct the impact analysis will be blinded to treatment assignment.

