##### Viral suppression

Our biological primary outcome will be a binary indicator for whether the participant has an undetectable viral load. The AIDS Clinical Trials Group defines virologic failure as a confirmed viral load > 200 copies/mL. We will consider that a viral load is undetectable if it is below 200 copies/mL. Viral load is the primary measure used to assess the level of viral activity in a person’s blood, as well as their response to ART. Although other factors besides adherence contribute to viral load, having an undetectable viral load is widely considered a strong indicator of good ART adherence. Furthermore, given the limitations of measures of behavioral adherence, viral load is considered by some to be the best indicator of adherence, and at the very least a valuable complement to behavioral adherence measures. Viral load measurements are now– part of routine clinical care at Mildmay and results for participants will be taken from clinical records. Viral load is measured when a person receives a positive HIV test result, after 6 and 12 months, and then every 12 months. We will synchronize recruitment so that the viral load of all participants is assessed at baseline, around month 12, and around month 24.

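### The adjusted viral-suppression model uses baseline viral load only as a yes/no indicator and forgoes a small amount of precision in the adjusted risk differences

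*Protocol article*

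**What the plan says.** The section Estimating impact on viral suppression plans an unadjusted logistic model (Eq. 1) and "a model that includes prespecified covariates to adjust for baseline characteristics and improve precision" (Eq. 2). The ten listed covariates include "baseline adherence, baseline WHO disease stage, baseline viral suppression, duration on ART". No continuous baseline viral load is listed, and no reason is given for using the binary form alone. The section names β1 and β2 as the coefficients of interest and also plans risk differences between each pair of arms.

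The section Viral suppression fixes the cut: "We will consider that a viral load is undetectable if it is below 200 copies/mL". It also says where the values come from and when: "results for participants will be taken from clinical records", and "We will synchronize recruitment so that the viral load of all participants is assessed at baseline, around month 12, and around month 24". The abstract states: "Secondary outcomes are the log-transformed viral load as a continuous measure". Numeric values are therefore expected to be on file.

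Under Randomization, viral load is a stratification factor, again with two levels. Under Sample size and power, the detectable differences are described as probably conservative because covariates will sharpen the estimates.

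**The concern.** Adjustment is justified here by precision, and the baseline value of the outcome variable is usually among the most useful covariates. Cutting it at 200 copies/mL gives a client at 250 copies/mL and one at 250,000 copies/mL the same covariate value, although their chances of later falling below 200 are unlikely to be equal. Eligibility rests on recent adherence problems, one form of which is lack of suppression, so some participants will start unsuppressed. Those are the participants for whom the copy number carries extra information. The two-level randomisation stratum does not balance copy number within the unsuppressed group either.

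At stake is efficiency only: somewhat wider intervals for the adjusted risk differences, and somewhat less power, than the collected data allow.

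**Working it through.** **1. The plan's own figure.** The article gives no figure for the gain from adjustment. Its nearest figure is the detectable difference at month 12, pooled arms against control: 7 percentage points. Inputs: 70% suppression in controls, 110 per arm less 10% attrition (99 control, 198 pooled), 80% power, two-sided; α is not stated, so 0.05 is assumed. The usual two-proportion formula with pooled variance under the null gives 14.2 points, not 7. That discrepancy is a separate matter, which this point neither depends on nor repairs. I use 14.2 only as the starting value in step 2.

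**2. Large-sample approximation.** Let R²(bin) be the outcome variance explained by the indicator alone, and R²(full) that explained by the indicator plus log10 copies among the unsuppressed. Then

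- variance ratio = (1 − R²(full)) / (1 − R²(bin));
- ratio of standard errors, or of detectable differences = square root of that.

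Assumed, because the documents do not give them: 30-70% suppressed at baseline; log10 copies among the unsuppressed with mean 4 and SD 1; odds ratio of 4 or 8 for the indicator; odds of later suppression falling by a factor of 1.0 to 3.0 per log10.

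Example with 50% suppressed and odds ratio 8 (detectable difference = 14.2 × √(1 − R²)):

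| Factor per log10 | R²(bin) | R²(full) | Variance ratio | SE ratio | Detectable difference |
|---|---|---|---|---|---|
| 1.0 | 0.175 | 0.175 | 1.000 | 1.000 | 12.9 |
| 1.5 | 0.176 | 0.197 | 0.975 | 0.987 | 12.7 |
| 2.0 | 0.175 | 0.231 | 0.933 | 0.966 | 12.4 |
| 3.0 | 0.175 | 0.290 | 0.861 | 0.928 | 12.0 |

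Over the whole grid, the variance ratio is 1.00 (factor 1.0), 0.97-0.99 (1.5), 0.92-0.96 (2.0) and 0.83-0.93 (3.0). The lowest SE ratio, 0.91, comes from one corner: 30% suppressed, factor 3, nothing else in the model.

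**3. Simulation.** 3,000 trials of 297 participants per scenario, pooled arms against control, logistic model with standardised risk difference. Both models carry a baseline adherence covariate (odds ratio 1.5 per SD). The indicator has odds ratio 6 and treatment odds ratio 2.3. Each cell shows indicator only → indicator plus log10 copies.

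| Suppressed at baseline | Factor | SD of risk difference | Ratio | Power | SE of log odds ratio |
|---|---|---|---|---|---|
| 50% | 1.0 | 0.0488 → 0.0489 | 1.00 | 0.749 → 0.750 | 0.319 → 0.321 |
| 50% | 1.5 | 0.0494 → 0.0489 | 0.99 | 0.753 → 0.761 | 0.319 → 0.325 |
| 50% | 2.0 | 0.0484 → 0.0471 | 0.97 | 0.718 → 0.739 | 0.318 → 0.332 |
| 50% | 3.0 | 0.0500 → 0.0467 | 0.93 | 0.634 → 0.682 | 0.316 → 0.345 |
| 70% | 1.5 | 0.0496 → 0.0494 | 0.995 | 0.737 → 0.739 | 0.323 → 0.327 |
| 70% | 2.0 | 0.0491 → 0.0482 | 0.98 | 0.725 → 0.741 | 0.322 → 0.331 |
| 30% | 2.0 | 0.0517 → 0.0498 | 0.96 | 0.709 → 0.747 | 0.309 → 0.325 |

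The standard error of the risk difference falls by 0-7% and power rises by 0-5 points. The standard error of the log odds ratio rises in every row. That is normal in logistic regression when a covariate is added: the coefficient also moves away from zero, so power does not fall.

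**4. Less favourable assumptions.** A second simulation (1,500 trials per scenario, n = 267, adherence covariate correlated with viral load) used odds ratios of 0.7, 0.5 and 0.35 per log10. With 30% detectable at baseline, the SD of the risk difference fell by 0.1%, 1.4% and 3.9%; with a baseline reliability of 0.6, by 0-0.5%. With 40-60% detectable it fell by 0.2-4.5%, or 0.1-3.6% at reliability 0.6. This is why 0-4% is the more plausible band.

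**The case against.** The strongest reply is that nothing here is wrong. The plan adjusts for the baseline value of its primary outcome, on the outcome's own scale and in the form used for stratification. That is a standard, valid choice, and refining one of ten covariates is optimisation. This stands, and it makes the fix optional.

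The size also rests wholly on assumptions. The documents give neither a prognostic slope nor the share detectable at baseline. Clients may qualify through adherence counselling or WHO stage without a detectable load. The baseline test may be up to 3 months from enrolment, and the intervention starts a further 2-3 months later, which weakens a single copy number. Baseline adherence, already in the model, may carry part of the same information. All of this stands and pulls the gain towards the low end, possibly to zero.

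Four stronger readings are tempting, and the documents do not support them:

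- *Chance imbalance in copy number biases the result.* It does not. Randomisation covers it, and the standard error already reflects it.
- *All treatment estimates become more precise.* The gain is in the risk differences and in power; the standard errors of β1 and β2 rise.
- *The saving is worth a tenth or more of the sample.* An SE ratio of 0.933 equals 1/0.933² = 1.15 times the participants, but only at the steepest assumed slope. At a factor of 1.5 it is 1/0.99² = 1.02.
- *The log viral load analysis is weakened in the same way.* The article shows no model or covariate list for that secondary outcome, so there is nothing to criticise.

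What survives the reply is narrow: the list is stated, precision is a stated purpose, the finer value is on file, and with no prognostic slope the extra term cost nothing measurable (ratio 1.00).

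**Conclusion.** The point holds as a minor efficiency point limited to the adjusted risk differences from Eq. 2. Adding the copy number would lower their standard error by about 0-7%, plausibly 0-4%, and raise power by about 0-5 percentage points. The direction depends on copy number being prognostic among the unsuppressed. The size depends on the assumed slope, the share unsuppressed at baseline and how current the baseline test is, none of which the documents give. The simulations in step 3 used the pooled contrast; a similar proportional gain for the arm-by-arm contrasts is expected but was not simulated. The plan's model remains valid as written.

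**What to change.** Optional. In Estimating impact on viral suppression, keep the baseline suppression indicator, because it is a stratification factor, and add *baseline log10 viral load, set to a constant when below 200 copies/mL* to the covariates of Eq. 2. With the indicator in the model, the choice of constant only shifts the indicator's coefficient and leaves the treatment estimates unchanged, so values below the cut need no imputation. Eq. 4 is defined by reference to the same covariates, so say whether the new term carries over; its effect there was not assessed. Prespecify the term before analysis, since a later addition would look data-driven. The cost is one degree of freedom and one line of text, with no new data.

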##### Estimating impact on adherence

To estimate the impact of our interventions on treatment adherence, we will use an ordinary least squares regression of the following forms:

Unadjusted:
3$$ {y}_{it}={\beta}_0+{\beta}_1T{1}_{it}+{\beta}_2T{2}_{it}+{\lambda}_t+{\epsilon}_i $$

Adjusted:
4$$ {y}_{it}={\beta}_0+{\beta}_1T{1}_{it}+{\beta}_2T{2}_{it}+{\lambda}_t+{\boldsymbol{X}}_{\boldsymbol{i}}\boldsymbol{\alpha} +{\epsilon}_i $$

where *y*_*it*_ represents the proportion of the prescribed bottle openings that were opened by individual *i* at time *t*. In this model, *β*_1_ represents the impact of T1 on the proportion of pills taken in a given month and *β*_2_ represents the impact of T2 on the proportion of pills taken in a given month. *λ*_*t*_ represents an indicator for each time period. Equation 4 includes the term ***X***_***i***_, which represents the same covariates as in Eq. 2.

##### Estimating impact on measured adherence over time

We will have a consecutive real-time measure of adherence for the duration of the study, which allows us to study adherence over time. To estimate the impact of the interventions on adherence over time, we will use the following ordinary least squares model:
5$$ {y}_{it}={\beta}_0+\sum \limits_{t=1}^{24}{\lambda}_t\left(T{1}_{it}\times {\mathrm{Month}}_t\right)+\sum \limits_{t=2}^{24}{\delta}_t\left(T{2}_{it}\times {\mathrm{Month}}_t\right)+\sum \limits_{t=1}^{24}{\mathrm{Month}}_t+{\epsilon}_i $$

where *y*_*it*_ represents the proportion of the prescribed bottle openings that were actually opened by individual *i* in month *t*. In this model, the *λ*_*t*_’s represent the impact of T1 at study month *t* and the *δ*_*t*_’s represent the impact of T2 at study month *t*.

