### Sampling and participants

We will recruit into the study 330 treatment-mature Mildmay clients. We have recruited patients at Mildmay in our previous studies without significant problems, and we have an ongoing collaboration with the medical records team that allows us to react swiftly to any problems. Indeed, we were able to recruit the target number of clients in less time than originally envisioned in previous studies.

Clinical records and the electronic database will be used to identify eligible clients. The inclusion criteria are described below. Clinic staff (rather than the study coordinator) will mine the clinic database for eligible clients, given that the client at that point has not yet consented to participating in the study. We will then recruit participants from the universe of eligible patients. This approach avoids many of the disadvantages of convenience sampling, such as the bias that may arise from sampling those most easily accessible.

Once eligible clients are identified in the database, the study team will use the next appointment as an opportunity for recruitment. Each day, the study coordinators will identify patients who are due for a visit that day and approach all those deemed eligible. Once a participant is located, the coordinator will initiate the pre-baseline visit by approaching them and inquiring whether they are interested in participating in an ongoing study. Respondents will also be informed that they will not lose their spot in the queue for seeing a provider. Patients who initially agree will be taken to a separate study room to verify their eligibility. We will then get consent from the patient to participate in the study. Once the participant gives consent, we will give them a medication event management system (MEMS) cap and instruct them to store all their HIV medication in a pill bottle with the MEMS cap attached. This MEMS cap will be used to record adherence, and participants will be asked to return with the MEMS cap at their next scheduled study visit in approximately 2–3 months, so the study team can retrieve their adherence data. These first 2–3 months of adherence data will be used as a baseline and the intervention will not begin before this follow-up visit.

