### Sample size and power

We have calculated the size of effects that our sample will be able to detect with 80% power (two-tailed test) with regard to outcomes at months 12 and 24, and 10% attrition every year (we observed 5% attrition over 20 months in our previous studies so this is a conservative estimate). For the primary outcome of viral suppression, we use a conservative estimate of 70% of clients in the control group showing suppression, based on discussions with the Mildmay team. Our sample size of 110 participants in each of the three arms (total *n* = 330) will be able to detect a 7 percentage point difference for joint comparison of T1 and T2 against the control group at month 12, and about an 8.5 percentage point difference between the two intervention arms (a subgroup analysis). The corresponding differences at month 24 are 8 and 9 percentage points, respectively. These are considered small effect sizes (Cohen’s *d* of between .15 and .185), which we will be able to detect. For adherence, in our previous study we observed mean adherence rates of ~75% as measured by MEMS caps. Our sample size of 110 in each of the intervention arms and the control group will provide sufficient power to detect about a 6.5 percentage point difference in mean adherence between the two intervention arms (combined) and the control group. To test for differences in adherence between the two intervention arms, our study is powered to detect about a 7.5 percentage point effect as measured by MEMS caps. Again, this means we will be able to detect small effects. The corresponding differences we will be able to detect at month 24 are about 7 and 8 percentage points, respectively. Our main econometric models will include covariates that will improve precision. Therefore, these minimum detectable effects reported above are likely upper bounds.

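### The month-by-month adherence model (Eq. 5) omits the baseline adherence that Eqs. 2 and 4 adjust for, so its monthly effects are unbiased but less precise than the data allow (minor; free improvement)

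*Protocol article*

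**What the plan says.** **The baseline exists.** Under Sampling and participants, the protocol article says of the first 2–3 months of MEMS recording: "months of adherence data will be used as a baseline and the intervention will not begin before this follow-up visit". The Design section repeats that adherence is recorded before the intervention for all participants. The rule excluding people who opened the cap on fewer than 30% of days also requires a run-in record for each person kept.

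**It is used in the other adjusted models.** Under Estimating impact on viral suppression, the covariate list begins: "We will adjust for the following covariates: age, education, sex, baseline adherence, baseline WHO disease stage, baseline viral suppression, duration on ART". Eq. 2 is the adjusted partner of Eq. 1. Under Estimating impact on adherence, Eq. 4 is the adjusted partner of Eq. 3 and takes the same covariates. Eqs. 3 and 4 give one coefficient per arm across all months.

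**It is absent from the time-course model.** Under Estimating impact on measured adherence over time: "To estimate the impact of the interventions on adherence over time, we will use the following ordinary least squares model". Eq. 5 has an intercept, T1-by-month terms, T2-by-month terms, month indicators and an error. There is no covariate vector and no second, adjusted form.

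**The power section.** The detectable differences are given for "80% power (two-tailed test) with regard to outcomes at months 12 and 24, and 10% attrition every year". For adherence they are 6.5 points (both incentive arms against control) and 7.5 points (between incentive arms), then 7 and 8 points at month 24. The section adds: "Our main econometric models will include covariates that will improve precision", and concludes that the quoted differences are probably on the pessimistic side.

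**The concern.** Earlier adherence measured by the same device is usually a good predictor of later adherence. A model that ignores it leaves the predictable between-person variation, and any chance difference between arms at baseline, in every monthly estimate. Stratification does not remove that difference, because the strata are age, sex, marital status, CD4 count and viral load, not adherence.

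The article prints the model and commits to it, so this is a stated choice and not a detail left for later. It also departs from the article's own practice of pairing an unadjusted with an adjusted model. What is at stake is the width of the monthly intervals. If the adherence figures in the power section mean adherence in month 12 and in month 24 taken singly, the argument that covariates make those figures conservative is also at stake, because the only model giving single-month effects has no covariates.

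**Working it through.** **Inputs from the document:** 110 per arm; 10% attrition per year; 80% power, two-tailed; the four adherence differences above.

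**Inputs not in the document:** the significance level (5% two-sided assumed), the SD of adherence (back-solved below), and the correlation ρ between baseline and month-t adherence (range shown).

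**Step 1. Reproduce the stated differences.** Retained per arm: 110 × 0.90 = 99 at month 12 and 110 × 0.81 = 89.1 at month 24. The pooled incentive group is twice that. For two means,

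detectable difference = (1.960 + 0.842) × SD × √(1/n₁ + 1/n₂).

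| Contrast | Multiplier of SD | Stated | Implied SD | At SD 19 |
|---|---|---|---|---|
| Month 12, pooled vs control | 0.345 | 6.5 | 18.8 | 6.55 |
| Month 12, T1 vs T2 | 0.398 | 7.5 | 18.8 | 7.57 |
| Month 24, pooled vs control | 0.364 | 7 | 19.3 | 6.91 |
| Month 24, T1 vs T2 | 0.420 | 8 | 19.1 | 7.98 |

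One SD of about 19 points fits all four. The stated figures are therefore consistent with an unadjusted two-sample comparison. Because the SD is back-solved, this shows internal agreement, not an independent reproduction.

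**Step 2. What Eq. 5 estimates.** With no covariates, its arm coefficient at month 12 or month 24 is the difference in arm means in that month. It gains no precision beyond an unadjusted comparison.

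**Step 3. Effect of adding baseline adherence.** The standard error is multiplied by √(1 − ρ²). Where unadjusted power is 80%, adjusted power = Φ(2.802/√(1 − ρ²) − 1.960). The equivalent gain in sample size is 1/(1 − ρ²).

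| ρ (assumed) | SE factor | Power from 80% | Equivalent sample size |
|---|---|---|---|
| 0.1 | 0.995 | about 80% | × 1.01 |
| 0.3 | 0.954 | about 84% | × 1.10 |
| 0.5 | 0.866 | about 90% | × 1.33 |
| 0.7 | 0.714 | about 97.5% | × 1.96 |

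If the SD of 19 applies to a single month, the detectable differences become (pooled; between arms):

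| ρ | Month 12 | Month 24 |
|---|---|---|
| 0 | 6.55; 7.57 | 6.91; 7.98 |
| 0.3 | 6.25; 7.22 | 6.59; 7.61 |
| 0.5 | 5.67; 6.55 | 5.98; 6.91 |
| 0.7 | 4.68; 5.40 | 4.93; 5.70 |

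**Step 4. Check by simulation.** Fitting the monthly model with and without a baseline term (3,000 runs per scenario) cut the standard error at months 12 and 24 by up to 1% at a correlation near 0.1, about 3% near 0.22, about 8% near 0.39 and about 16% near 0.54. This agrees with the formula.

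**Step 5. One slope or a slope per month.** If the correlation fades, a single baseline slope b gives an SE factor of √(1 − 2bρ + b²). With b = 0.5 and ρ = 0.4 at month 24 this is √(1 − 0.4 + 0.25) = 0.922, against √(1 − 0.16) = 0.917 with a month-specific slope. With b = 0.45 and ρ = 0.3 the factors are 0.966 and 0.954. The month-specific slope is a modest safeguard.

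**The case against.** The strongest reply is that the main adherence analysis is Eq. 4, and it already adjusts for baseline adherence. Eq. 5 stands under its own heading as a time-course analysis. The power section promises covariates only in the main models, and Eqs. 2 and 4 keep that promise. This stands: the document does not contradict itself, and the averaged adherence effect loses nothing.

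A reader might go further and infer that Eq. 5 is the model behind the adherence power figures, so that the power claim is unsupported. The text does not establish this. It does not say whether adherence at month 12 or 24 means that one month or the average up to it, and the behavioural primary outcome is not tied to a single calendar month. If averages are meant, Eq. 4 fitted up to those times delivers them with baseline adjusted. The SD of 19 would then not describe a single month either. The √(1 − ρ²) factors would be unaffected.

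The size of the gain is also open. Participants are selected for recent adherence problems and for at least 30% cap use, which may narrow the baseline range and lower ρ. A 2–3 month baseline must also predict a single month up to two years later. This stands too, so the range is reported and no single value is put forward.

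Finally, an adjusted time-course model might be left to an analysis plan. That carries less weight here, because the article prints a specific equation and commits to it.

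**Conclusion.** The point holds as a minor one. As printed, Eq. 5 gives unbiased month-by-month adherence effects that are less precise than the collected data allow.

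The gain forgone ranges from negligible (ρ near 0.1) to substantial (ρ of 0.5 or more). The standard-error figures rest on the assumed ρ; the power figures rest also on an assumed two-sided 5% level and an unadjusted power of 80% for the contrast concerned.

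The bearing on the power section is conditional. If its adherence figures refer to single months, Eq. 5 does not support calling them conservative; if they refer to averages up to those months, Eq. 4 does. A reader might also take disagreement between the monthly curve and the Eq. 4 effect as a sign of error. It would not be: adjusted and unadjusted estimates differ by chance, and the article plans to report both kinds elsewhere.

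**What to change.** Add an adjusted version of Eq. 5, parallel to Eq. 4, containing the prespecified covariates, with pre-intervention MEMS adherence entered both as a main term and in interaction with month. Keep the printed Eq. 5 as the unadjusted companion. State in the power section whether adherence at months 12 and 24 means the single month or the average up to it, and name the model that estimates it.

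The cost is a sentence or two and a few regression terms. The data are already collected and already used in Eq. 4, so no patients, visits or tests are added. Any participant without a usable run-in value would need simple imputation of the covariate, which should be rare given the cap-use rule. The change should be fixed before the outcome data are analysed, so that adjustment is not chosen after the curves have been seen.
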